### Trial design {8}

This is the protocol of a parallel-group, controlled, randomized trial, with a pre-post and repeated follow-up measures between-group design.

A three-arm trial is going to be carried out. Participants who meet the recruitment criteria bellow will be randomly assigned to Group 1: Water exercise group, Group 2: Land exercise group, or Group 3: Control group. The assessment will be conducted at five-time points: an initial assessment before being randomized (pretreatment; T0), at the end of the intervention (post-treatment; T1), 3 months after the completion of the intervention (T2), 12 months after the completion of the intervention (T3), and 24 months after the completion of the intervention (T4). CONSORT patient’s flowchart is presented in Fig. 1.

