### Sample size {14}

One hundred and fifty cancer patients aged 18–65 years (stage III colon cancer patients and breast cancer patients with lymph node involvement) will be recruited via advertisements in Hadassah Medical Center and Tal Aviv University. The sample size is based on data from the WHO Disability Assessment Schedule (WHODAS 2.0), which has been used internationally to assess function and disability among a healthy population versus an unhealthy population [26]. The expected difference in the questionnaire scores between the two groups is 15 points and the average standard deviation is 15.08. The sample calculation includes a type 1 error of alpha equal to 0.05 with a power of 80%. According to this calculation, 16 participants are needed in each of the three study groups. Because we anticipate the withdrawal of some of the participants and because of the clinical condition of all participants, a number of 50 participants per group was selected.

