### Assignment of interventions: allocation

#### Sequence generation {16a}

Simple randomization will be used in this study. Participants who met the inclusion criteria will be randomized to one of three groups, using specific online software (https://www.randomizer.org/). Ratio allocation will be 1:1:1 (approximately).

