### Statistical methods

#### Statistical methods for primary and secondary outcomes {20a}

Every participant will be assigned a random study identifier number, ensuring the privacy of their personal data. The statistical analyses will be conducted in a way that prevents the identification of individual patients. We will conduct a series of mixed variance analyses to identify relationships and associations between groups, as well as changes over time within each group (independent variables). The dependent variables will be primary and secondary outcomes, and a separate analysis will be performed for each variable.

Additionally, we will conduct various analyses to explore the relationships between changes in the dependent variables.

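### A group-by-time mixed ANOVA that includes the pre-randomisation score is valid, but less precise than a baseline-adjusted model of the follow-up scores

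*Protocol article*

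**What the plan says.** All references are to the protocol article.

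- **Statistical methods {20a}** plans a series of mixed variance analyses, one per outcome. The sentence that names the model covers associations between groups "as well as changes over time within each group (independent variables"). No covariate is named. The abstract describes the same model.
- **Trial design {8}** describes a pre-post, repeated-measures, between-group design. The first of its five time points is "an initial assessment before being randomized (pretreatment; T0"), followed by T1 to T4.
- **Sample size {14}** works from WHODAS 2.0: "The expected difference in the questionnaire scores between the two groups is 15 points", "the average standard deviation is 15.08", and "16 participants are needed in each of the three study groups". Fifty per group was then chosen to allow for withdrawals.
- **Eligibility criteria {10}** recruits within 3 months of the end of chemotherapy. **Intervention description {11a}** includes a control group with no added exercise.
- **Sequence generation {16a}** states: "Simple randomization will be used in this study".

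**The concern.** A score taken before randomisation cannot respond to treatment. If it is a level of the time factor, two things follow:

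- The group main effect averages in one visit at which the arms cannot differ through treatment.
- The group-by-time term works like a comparison of change from baseline. That subtracts the whole baseline score, rather than the fraction of it that predicts follow-up.

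Both use the data less well than adjusting for baseline, at no saving in cost or effort. What is at stake is power for effects smaller than the planned 15 points, and after withdrawals.

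There is also a question of interpretation. The sentence on analysis puts change within each group beside the between-group comparison and does not mark it as descriptive. Patients who have recently finished chemotherapy may improve without exercise, so improvement within an arm says nothing about the programme.

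**Working it through.** **Inputs.** From Sample size {14}: difference 15, SD 15.08, alpha 0.05, power 80%, 50 per arm. Assumed, because the article does not give them: the correlation r between any two visits (0.3 to 0.7, equal for all pairs), equal SD at all visits, a smaller effect of 7 points constant over T1 to T4, and no loss to follow-up. All tests are two-sided at 0.05. Power uses the normal approximation for two arms unless stated.

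**1. The protocol's own figure.** n = 2 × (15.08 × (1.960 + 0.842) / 15)² = 15.87, so 16 per group. The stated figure reproduces. It is a calculation for a single score in two groups and uses no baseline information.

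**2. One follow-up visit.** In units of SD², the variance is 2(1−r) for change from baseline and 1−r² for the baseline-adjusted score. The ratio is (1−r²) / (2(1−r)) = (1+r)/2:

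| r | ratio | detectable difference at 50 per arm, 80% power: change | adjusted |
|---|---|---|---|
| 0.3 | 0.65 | 10.0 | 8.1 |
| 0.5 | 0.75 | 8.5 | 7.3 |
| 0.7 | 0.85 | 6.6 | 6.0 |

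The ratio is below 1 for every r below 1.

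**3. All visits, like for like.** In units of SD²:

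- Group main effect over T0 to T4: variance (1+4r)/5, with the effect diluted to 4/5 of its size.
- Mean of T1 to T4 minus T0: variance (1+3r)/4 + 1 − 2r.
- Mean of T1 to T4 adjusted for T0: variance (1+3r)/4 − r².

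Power = Φ(effect / (15.08 × √(2 × variance / 50)) − 1.96).

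Example at r=0.6 with 7 points:

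- Main effect: variance 0.68, SE 2.487, 5.6/2.487 = 2.25, power 61%.
- Mean follow-up minus baseline: variance 0.50, SE 2.133, 7/2.133 = 3.28, power 91%.
- Baseline-adjusted mean follow-up: variance 0.34, SE 1.759, 7/1.759 = 3.98, power 98%.

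| r | group main effect | mean follow-up minus baseline | baseline-adjusted mean follow-up |
|---|---|---|---|
| 0.3 | 80% | 70% | 96% |
| 0.5 | 67% | 84% | 97% |
| 0.6 | 61% | 91% | 98% |
| 0.7 | 57% | 97% | 99% |

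The omnibus group-by-time test has (3−1) × (5−1) = 8 degrees of freedom. If one arm differs from the other two by 7 points at every follow-up visit, its noncentrality at r=0.6 is 50 × (49 × 2/3) × 0.8 / (15.08² × 0.4) = 14.4. Its power by the F distribution is about 77%.

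**4. At the protocol's 15 points.** For r from 0.3 to 0.7, all three approaches in the table have at least 99.5% power with 50 per arm. The lowest is the main effect at r=0.7: 12/2.629 = 4.56. A single-visit change score at r=0.3 still has 98.8% (15/3.569 = 4.20).

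**5. Within-arm change with no treatment effect.** Assume a natural recovery of 5 points in an arm of 50. The SE of the mean change is 15.08 × √(2(1−r)/50), which is 2.13 at r=0.5 and 1.65 at r=0.7. The chance of p<0.05 is 65% and 86%.

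**The case against.** **T0 as a response is inferred.** The article never says whether T0 is a level of time or a covariate, and a statistical analysis plan could settle it. This stands as a limit on certainty. But the model named, the pre-post label and the list of five time points all point to T0 as a level of time, and that is the design the article fixes.

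**The group-by-time test is valid.** With a randomised control arm, recovery common to all arms cancels out of it. This stands in full: the point is about precision, not bias. The group main effect is also not the natural treatment test in a pre-post design, so its 57% to 80% should not be read as the power of the planned analysis.

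**The within-group wording may only name the model factors.** The same sentence plans between-group associations, and all three objectives compare the water group with the other two. A reader might infer that improvement within an arm will be reported as benefit. No passage says so. What remains is that within-arm change is not marked as descriptive.

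**The loss depends on a small effect.** The 7 points are not in the article, and at 15 points nothing material is lost. This stands. A smaller effect is still a reasonable case to consider. The 15 points are tied to WHODAS data on healthy against unhealthy populations, whereas one planned comparison is water against the same movements on land. Withdrawals are also expected.

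**Simple randomisation.** A reader might infer that unstratified allocation with two cancer types is a flaw that needs correcting. At an assumed 50:50 mix there is a 30% chance that two arms differ by at least 15 percentage points in cancer type, falling to about 24% or 15% if the less common type makes up 30% or 20%. But simple randomisation is valid, chance imbalance is not bias, and the article does not show that cancer type predicts any outcome. Stratified blocks would be a preference for efficiency with no quantified gain.

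**Conclusion.** The concern holds as a moderate point of efficiency and interpretation. On the natural reading, the planned mixed ANOVA is valid but less precise than adjusting for the baseline score. With a 7-point effect, the like-for-like gain in power runs from about 26 percentage points at r=0.3 to about 2 or 3 at r=0.7. These figures rest on an assumed effect, an assumed common correlation, equal SDs and full follow-up of 50 per arm. The direction of the comparison with change from baseline does not depend on the value of r below 1. At the protocol's own 15 points the loss is negligible, so the stated target is not threatened.

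The article does not support two stronger conclusions: that the planned test is invalid, or that the randomisation must be changed.

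**What to change.** For each scale score, replace the mixed ANOVA by a linear mixed model of T1 to T4 with arm, visit, arm-by-visit, and the baseline score with a separate slope at each visit. Cancer type may be added as a covariate. Base conclusions on between-arm contrasts, either at named visits or averaged over follow-up, specified before the data are examined. State that change within an arm is descriptive only.

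The date of return to work has no baseline score of this kind and is outside this change. Simple randomisation can stay.

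The cost is analysis wording. The baseline scores are already collected and cancer type is known at recruitment, so no new data are needed. Because the article requires both ethics committees to approve any protocol change, the revised text would go through that step.

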**Methods:**

This randomized controlled trial will include 150 cancer patients aged 18–65 years with stage III colon cancer or breast cancer patients with lymph node involvement. Participants in the aquatic exercise intervention group will undergo an 8-week, twice-weekly group-based Ai-Chi program, while the on-land exercise group will perform identical exercise. The control group will not engage in any exercise.

The primary outcome will be assessed using an employment barriers questionnaire, capturing return to work date and working hours and daily life participation and activity and quality of life. Secondary outcomes include exhaustion, fatigue, and neuropathy. Data will be collected at baseline, post-intervention (8 weeks), and at 3,12, and 24 months. Mixed variance analyses will explore relationships among groups and over time for independent variables, with separate analyses for each dependent variable.

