### Primary outcome

Employment Barriers Questionnaire [25] and Date of return to work and duration of working hours—self-report by the study participants.WHODAS 2.0—to examine the degree of activity and participation in daily life [26].EORTC QLQ-C30—to evaluate the quality of life from the point of view of the participant [27].

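### Five co-equal primary outcomes are analysed separately with no hierarchy, success rule or primary time point, while the sample size spends the full 0.05 on one two-group WHODAS 2.0 comparison

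*Protocol article*

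**What the plan says.** All references are to the protocol article.

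- **Primary outcome.** Three employment measures come first: "Employment Barriers Questionnaire [25] and Date of return to work and duration of working hours". WHODAS 2.0 and the EORTC QLQ-C30 follow under the same heading. None is ranked above another, and no QLQ-C30 scale is chosen. The abstract speaks of one primary outcome but describes it as "capturing return to work date and working hours and daily life participation and activity and quality of life".
- **Trial design {8}.** There are three arms: "Group 1: Water exercise group, Group 2: Land exercise group, or Group 3: Control group". On timing, "The assessment will be conducted at five-time points", that is, baseline and four follow-up visits. No visit is marked as primary.
- **Statistical methods {20a}.** A mixed analysis of variance has group and time as its factors, and "a separate analysis will be performed for each variable". No rule says whether one, some or all primary outcomes must succeed, or which term of the model decides.
- **Sample size {14}.** The calculation uses WHODAS 2.0 only, with a 15-point difference between two groups and a standard deviation of 15.08. "The sample calculation includes a type 1 error of alpha equal to 0.05 with a power of 80" per cent. It arrives at 16 per group, and 50 per group are planned.

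**The concern.** The 5% error rate is stated once, for one comparison of one outcome. The analysis section then treats five outcomes as equally primary and gives each its own analysis. Nothing singles out the WHODAS 2.0 comparison as the decisive one, so the stated 5% is not the error rate of the trial's primary conclusion.

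Two things are at stake. First, a nominally significant result on any one of the five could be presented as a positive trial, at an error rate several times the nominal one. Second, if the five disagree, or if one outcome differs at 8 weeks but not at 12 months, the protocol gives no way to say whether the trial succeeded. The outcomes are self-reported and participants know their allocation, so fixing the deciding result in advance matters more than usual.

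**Working it through.** **1. The protocol's own figure.** Two groups, two-sided alpha 0.05, power 80%, difference 15, SD 15.08:

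n = 2 × (1.960 + 0.842)² × (15.08/15)² = 15.87, rounded up to 16 per group.

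This matches. A one-sided test gives 13. The 16 is therefore one two-sided, two-group comparison of one outcome at the full 0.05, with nothing set aside for four further primaries or a third arm.

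**2. Closest reading of the stated plan: one group test per outcome, five tests at 0.05.**

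- If independent: 1 − 0.95⁵ = 0.226.
- If correlated: simulated null trials with 3 arms of 50 give about 20% at a between-outcome correlation of 0.3 and 15% at 0.7.

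The article gives no correlations, so these are assumptions. The range is 15–23%, or three to four and a half times the nominal 5%.

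**3. What further testing would add.** The article states none of these; they show how far the rate depends on what is left open.

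| Tests counted as primary | Chance of at least one false positive | Assumptions |
|---|---|---|
| Group effect and group-by-time interaction, per outcome | 29–38% | outcome correlation 0.7 to 0.3, visit correlation 0.6 |
| Two water contrasts (versus land, versus control), per outcome | 26–38% | outcome correlation 0.7 to 0 |
| All three pairwise contrasts, per outcome | 33–48% | outcome correlation 0.7 to 0 |
| All three contrasts at each of four visits | 59–86% | outcome correlation 0.7 to 0.3, visit correlation 0.8 to 0.5 |

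The shortcut 1 − 0.95¹⁵ = 0.537 for five outcomes by three contrasts is not valid. Pairwise contrasts among three arms share arms and cannot be independent; with fully independent outcomes the simulated figure is 48%.

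**4. Cost of error control for WHODAS 2.0.** Holm's strictest level over five tests is 0.05/5 = 0.01.

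- Standard error with 50 per group: 15.08 × √(2/50) = 3.016, and 15/3.016 = 4.973.
- Two-group power at 0.01: Φ(4.973 − 2.576) = Φ(2.397) = 0.992.
- Global three-arm F test at 0.01, assuming the third arm lies midway: noncentrality 50 × (7.5² + 7.5²)/15.08² = 24.7 on 2 and 147 degrees of freedom, power about 0.98.
- Needed for 80% two-group power at 0.01: 2 × (2.576 + 0.842)² × (15.08/15)² = 23.6, so 24 per group. Of 50, 26 could be lost.

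These rest on the protocol's own 15-point assumption. No effect size is given for the other four primaries, so their power cannot be checked.

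**The case against.** The strongest reply is that this is a condensed article and the analysis plan is not shown. A multiplicity method, a contrast procedure or the choice of a QLQ-C30 scale could properly sit there. That is fair, and the absence of a named multiplicity method is not in itself the finding. What stands is that the choice of primary outcome and its time point belongs in the protocol. This protocol has made that choice: five equal primaries, analysed one by one, beside a sample size that treats one of them as the trial.

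A second reply is that the mixed model holds all arms and visits together for each outcome. This also stands, and it limits the claim. A reader might infer that three contrasts at four visits are each to be tested for five outcomes, so that a false positive is more likely than not. The article does not say this: it states separate analyses per outcome only. The objectives compare water with each of the other two groups, so land versus control is not an objective. Return-to-work date is one event per participant, not a fresh test at every visit. The higher figures in the table are therefore conditional.

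A third reply is that WHODAS 2.0 should not become the sole primary merely because it was used for the sample size. Return to work is objective A and the stated public benefit. That stands too, and the fix leaves the choice to the sponsor.

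**Conclusion.** The concern holds at the level of outcomes. Five co-equal primaries, each analysed separately, with no hierarchy, success rule or primary time point, do not fit a sample size that gives 0.05 to a single two-group WHODAS 2.0 comparison. Followed as written, with one group test per outcome, the chance of at least one false positive primary result is about 15–23% rather than 5%. The upper end assumes independent outcomes; the lower end assumes a correlation of 0.7. The rate rises if model terms, contrasts or visits are also counted as primary, but the article does not state that they are. That a false positive is likely is therefore not supported.

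**What to change.** **Preferred change.** Keep the five primaries, and:

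- name one primary time point (for return-to-work date, a follow-up cut-off) and one QLQ-C30 scale;
- test the three arms globally for each outcome, and apply Holm across the five global tests at an overall 0.05;
- only where the global test is significant, go on to the pairwise contrasts by a closed procedure within that outcome's Holm level. With exactly three arms, each contrast can then be tested at that level without further splitting.

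One limit should be written down. Holm protects the five global statements, and the closed procedure protects the contrasts within one outcome. Together they do not hold 5% over all contrasts of all outcomes: if all five global tests are rejected, the Holm levels add up to 0.01 + 0.0125 + 0.0167 + 0.025 + 0.05 = 0.114. If the contrasts are to be confirmatory across outcomes, use a fixed 0.01 for the global test and the contrasts of each outcome, which bounds the total at 5 × 0.01 = 0.05.

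**Alternative.** Name a single primary outcome at one time point, test globally at 0.05 and then pairwise as above, and make the rest secondary. WHODAS 2.0 is the only outcome with a size calculation; choosing return to work would need one.

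**Cost.** Fewer results can be called confirmatory. The change is an amendment to a trial that began recruiting in April 2023, and the section on protocol amendments {25} requires approval by both ethics committees first. It should be settled before outcome data are examined by arm. WHODAS 2.0 needs no extra participants under the protocol's own assumptions.

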### Interim analyses {21b}

No interim analysis will be carried out in this trial.

### Methods for additional analyses (e.g. subgroup analyses) {20b}

Additional analyses have not been planned.

### Methods in analysis to handle protocol non-adherence and any statistical methods to handle missing data {20c}

To address protocol non-adherence, intervention physiotherapists will receive intervention protocol. Missing data will be imputed using the random forest method.

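### The missing-data rule names random-forest imputation with no way to carry its uncertainty; if applied as a single fill, it understates standard errors or shrinks effects, depending on whether arm is a predictor

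*Protocol article*

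**What the plan says.** Section {20c} of the protocol article handles missing data in one sentence: "Missing data will be imputed using the random forest method". It does not give the number of imputed data sets, the predictors, whether arm is one of them, whether values are drawn at random or are plain predictions, or how variance is computed afterwards.

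Section {20a} describes the analysis: "We will conduct a series of mixed variance analyses to identify relationships and associations between groups, as well as changes over time within each group". Each outcome is analysed separately. Nothing is said about combining results over several completed data sets. Section {20b} states that no additional analyses are planned, so the article holds no sensitivity analysis that would act as a check.

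Three other sections bear on how much will be missing:

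- Sample size {14} calculates that "16 participants are needed in each of the three study groups" and then, citing expected withdrawal of some participants and their clinical condition, states that "a number of 50 participants per group was selected". No withdrawal rate is given.
- Trial design {8} places the last two assessments 12 and 24 months after the intervention ends.
- Sections {18a} and {18b} provide telephone interviews for missed visits, and e-mail and telephone contact to support follow-up.

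**The concern.** A random-forest prediction estimates a conditional mean. Put into a gap once, it lacks the scatter of a real observation, and the analysis that follows treats it as an observed value. Two errors result. The residual variance is too small because the filled values lie too close to their predictions. The sample also counts as complete although part of it carries no new information.

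In Rubin's notation the total variance is T = W + (1 + 1/M)B, where W is the average within-data-set variance, B the between-imputation variance and M the number of imputed sets. A single fill of predictions reports only a W that is itself too small, and omits B.

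A second problem concerns the treatment effect. A forest uses the arm indicator only in part, or not at all if it is not supplied. Filled values in different arms are then pulled towards each other, and so is the estimated difference.

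The rule covers the primary questionnaire outcomes. It would matter most at whichever visits have the most missing values, and long follow-up makes the 12- and 24-month visits the likely ones.

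**Working it through.** **The plan's own figure.** Inputs from Sample size {14}: difference 15, SD 15.08, alpha 0.05 (two-sided assumed), power 80%.

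n per arm = 2(z₀.₉₇₅ + z₀.₈₀)² × (SD/difference)² = 2 × (1.960 + 0.842)² × (15.08/15)² = 2 × 7.85 × 1.0107 = 15.87, so 16. This reproduces the stated number. The exact t-test needs 17 (power 77.7% at 16, 80.3% at 17). The calculation contains no allowance for imputation, so the consequence of {20c} was checked by simulation.

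**Set-up.** From the article: 50 per arm, SD 15.08, nominal 0.05. Assumed: two arms; four visits with equal correlation 0.3 or 0.6; only the last visit missing, completely at random, in 10-50%; comparison at the last visit adjusted for baseline. There were 800 runs per cell. The Monte Carlo error of a true 5% rate is √(0.05 × 0.95/800) = 0.0077.

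**No true difference, one random-forest fill.** Type 1 error, with mean reported SE divided by empirical SD in brackets:

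| Missing | Arm in forest, corr. 0.3 | Arm in forest, corr. 0.6 | Arm left out, corr. 0.3 / 0.6 |
|---|---|---|---|
| 10% | 0.058 (0.98) | 0.064 (0.95) | 0.044 / 0.048 |
| 20% | 0.062 (0.94) | 0.062 (0.93) | 0.035 / 0.041 |
| 30% | 0.098 (0.83) | 0.068 (0.92) | 0.048 / 0.046 |
| 50% | 0.138 (0.73) | 0.112 (0.80) | 0.048 / 0.050 |

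With arm left out, the SE ratio was 0.99-1.04 throughout. Complete cases gave 0.031-0.064. The rows agree with the rate implied by the SE ratio r, which is 2{1 − Φ(1.96r)}: for r = 0.83 it is 0.10, and for r = 0.92 it is 0.07. At 10-20% missing, no single cell is clearly separable from 5%: (0.064 − 0.050)/0.0077 = 1.8. At 30% with correlation 0.3 the excess is (0.098 − 0.050)/0.0077 = 6.2 Monte Carlo errors.

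**True 15-point effect at all follow-up visits, one fill.** Mean estimate, 100 runs per cell:

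| Missing | Arm in forest, corr. 0.3 / 0.6 | Arm left out, corr. 0.3 / 0.6 |
|---|---|---|
| 20% | 14.61 / 13.90 | 13.78 / 14.06 |
| 30% | 13.65 / 13.92 | 13.15 / 13.35 |
| 50% | 12.65 / 13.25 | 10.80 / 12.65 |

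With complete data the SE of the difference would be 15.08 × √(1 − ρ²) × √(2/50), which is 2.88 for ρ = 0.3 and 2.41 for ρ = 0.6. The Monte Carlo error of a mean over 100 runs is therefore roughly 0.25-0.3. Shrinkage below 15 is clear at 30% and 50%. The extra shrinkage from leaving arm out is clear only at 50% with correlation 0.3.

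**Second set-up.** Three arms of 50, five visits, correlation 0.6, dropout that is permanent once it occurs, arm in the forest, water versus land at the last visit. With 30% missing, mean reported SE was 2.14 against an empirical SD of 2.43 (ratio 0.88), with type 1 error 0.081 over 1,268 runs. With 20% missing, the figures were 2.23, 2.45 (ratio 0.91) and 0.070. A true 8-point effect was estimated at 7.48 (200 runs). Baseline-adjusted analysis of observed cases with 30% missing gave SE 2.91, empirical SD 2.92 and type 1 error 0.050.

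**A remedy checked.** In the first set-up, multiple imputation (20 sets, parameter and residual draws, arm in the model, Rubin's rules, 1,500 runs per cell) gave type 1 error 0.041-0.051 at 10-50% missing, with SE ratio 0.99-1.03. The imputation model was linear and Bayesian, not a random forest.

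**The case against.** The strongest reply is that the article never says the gaps are filled once. Random forest names the prediction engine and can be used within multiple imputation with random draws. The number of sets, the predictors and the pooling rule are details that an article may leave to an analysis plan, which is not at hand. This stands as far as it goes, and it is why the point is conditional. It does not remove the point. {20c} and {20a} together name a complete route from missing values to analysis, and that route contains no step that carries imputation uncertainty.

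Three stronger readings are tempting, and the article does not support them.

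- A reader might infer that intervals are certainly too narrow and false positives certainly inflated. With arm left out of the forest there was no inflation under the null, and at 10-20% missing the inflation is small even with arm included.
- A reader might take the step from 16 to 50 per arm as a forecast of heavy loss, since 1 − 16/50 = 68%. The article speaks of withdrawal by some participants, gives clinical condition as a second reason, and states no rate. Telephone collection and retention contact will lower missingness by an unknown amount.
- A reader might conclude that the planned analysis itself has been shown to fail for every outcome. Both simulations tested one late-visit comparison of one WHODAS-like score, not the full group-by-time mixed analysis of variance.

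**Conclusion.** The concern holds conditionally, with moderate confidence. Applied as a single fill, which the text suggests but does not state, the rule does harm whichever way arm is handled. With arm in the forest, standard errors are too small and type 1 error rises with the share missing, while effects shrink modestly. With arm left out, type 1 error is kept, but true effects are diluted, generally somewhat more. The article does not let a reader tell which would apply.

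The size rests on assumed missing rates and correlations and, in the first set-up, on values missing completely at random. Below about 20% missing the effect on type 1 error is minor; from 30% upwards it is material. Where T3 and T4 will fall on that scale cannot be settled from the article. If multiple imputation is already intended, stating so with its pooling rule would close the point.

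**What to change.** For the repeated outcome scores, replace imputation followed by mixed analysis of variance with a likelihood-based linear mixed model. Fit it to all observed T1-T4 values, with baseline as covariate and arm, visit and arm-by-visit terms. It needs no imputed outcomes and is valid if data are missing at random.

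If random forest is to be kept, specify it within multiple imputation: at least 20 sets, random draws rather than plain predictions, arm and all visits in the imputation model, and results combined by Rubin's rules. A delta-shift sensitivity analysis, which moves imputed values by a stated amount, would be a useful optional addition.

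The cost is analysis wording and wider intervals. In the second set-up with 30% missing, observed-case analysis reported an SE of 2.91 against 2.14 for the single fill, a ratio of 2.91/2.14 = 1.36. Part of that gap is the understatement being removed. The mixed model also uses the earlier follow-up visits and should lose less precision than observed cases alone, but it was not simulated here. Recruitment is expected to run until August 2027 and no interim analysis is planned, so the change can be made before any comparative analysis.
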